## Abstract

**Background:**

Making fun of growing older is considered socially acceptable, yet ageist humour reinforces negative stereotypes that growing old is linked with physical and mental deterioration, dependence, and less social value. Such stereotypes and discrimination affect the wellbeing of older people, the largest demographic of Canadians. While ageism extends throughout professions and social institutions, we expect nurses—the largest and most trusted group of healthcare professionals—to provide non-ageist care to older people. Unfortunately, nurses working with older people often embrace ageist beliefs and nursing education programs do not address sufficient anti-ageism content despite gerontological nursing standards and competencies.

**Methods:**

To raise awareness of ageism in Canada, this quasi-experimental study will be supported by partnerships between older Canadians, advocacy organizations, and academic gerontological experts which will serve as an advisory group. The study, guided by social learning theory, will unfold in two parts. In Phase 1, we will use student nurses as a test case to determine if negative stereotypes and ageist perceptions can be addressed through three innovative e-learning activities. The activities employ gamification, videos, and simulations to: (1) provide accurate general information about older people, (2) model management of responsive behaviours in older people with cognitive impairment, and (3) dispel negative stereotypes about older people as dependent and incontinent. In Phase 2, the test case findings will be shared with the advisory group to develop a range of knowledge mobilization strategies to dispel ageism among healthcare professionals and the public. We will implement key short term strategies.

**Discussion:**

Findings will generate knowledge on the effectiveness of the e-learning activities in improving student nurses’ perceptions about older people. The e-learning learning activities will help student nurses acquire much-needed gerontological knowledge and skills. The strength of this project is in its plan to engage a wide array of stakeholders who will mobilize the phase I findings and advocate for positive perspectives and accurate knowledge about aging—older Canadians, partner organizations (Canadian Gerontological Nurses Association, CanAge, AgeWell), and gerontological experts.

Contributions to the literature
Ageism in Canada extends through many organizations and institutions, including healthcare. This study will build knowledge on the effectiveness of e-learning approaches in dispelling ageist misconceptions amongst student nurses.This study will generate evidence on the effectiveness of the three e-learning activities on student nurses’ perceptions of older people.This study’s partnership approach to knowledge mobilization can guide researchers seeking to involve key stakeholders and community-members in the development and implementation of strategies to improve healthcare education and delivery, enacting positive social change.

## Background

### Understanding ageism

Canada has more people aged 65 and older than it has children 14 and younger [1], with ageism impacting many of these older Canadians. Butler [2] defines ageism as negative perceptions attributed to a population based on its age. Ageism includes negative attitudes towards older people, aging, and the aging process, as well as discrimination that is either individual or systemic [3]. Stereotypes of growing old include increasing illness, isolation, poverty, and depression contribute to ageism [4]. Further, negativity towards older people is accepted, without social sanctions [5], with the result that it flourishes in Canada. Ageism often emerges “insidiously, veiled in claims of ‘best interest,’ or humor” ([6] p. 644), as a socially acceptable form of discrimination. Most older Canadians live independently in the community and growing numbers continue to work after the age of 65 [7, 8]. Unfortunately, they experience ageism when purchasing goods and services [9], in their familial relationships [10] and in healthcare institutions [11].

#### Impacts of ageism

Research has demonstrated a negative association between age discrimination and older people’s well-being [12] and self-esteem [13], and a positive association with depressive symptoms [14]. This suggests that negative stereotypes about aging can become internalized [13, 14], so that conscious or unconscious ageist perceptions and stereotypes influence the cognitive and/or physical functioning of older people and erode their will to live [15]. Various international studies have reported the deleterious effects of ageism: healthcare costs in the United States due to health-related illness from ageism are estimated at $63 billion a year [16]. European-based studies have reported that older people are treated negatively and undervalued [17, 18]. A 2008 Canadian study involving people of all ages reported that, regardless of culture and religious philosophy, Canadians view older people as “less vital” and “non-accommodating” ([19] p. 28); the study also revealed that younger Canadians respect older people but want to avoid them.

#### Aging in a nursing context

Palmore [20] has called ageism a “virus” ingrained into cultures, so pervasive that even older people have negative stereotypes of aging. Thus, it is not surprising that ageism, in the form of poor care of older people, persists within healthcare, despite initiatives to improve their care and status [6]. Healthcare systems are designed for younger people, emphasizing efficiency and quick turnover, and do not consider the complexity of older people’s health and social concerns [11, 21]. This ageist perspective extends to the nursing profession, the largest group of healthcare professionals [22], with many nurses believing that working with older people is of low occupational status [23]. Scholars have suggested that nurses’ ageist stereotypes exist because they see older people at their most vulnerable and dependent [24–26]. Additionally, when nurses hold negative stereotypes of cognitive and physical decline of older people [3]—and believe that working with older people is simple [24–26]—they fail to adequately assess and manage older people’s healthcare concerns, leading to negative consequences [25, 27–31]. Conversely, when nurses have positive perceptions of older people, they are more likely to recognize older people’s health and social needs and meet them appropriately [19, 32].

A recent review of gerontological competency frameworks in Canadian health and social service education suggests the need for greater gerontological competencies across professions [33]. Canadian gerontological experts have developed gerontological competencies for nursing programs [34], and professional gerontological nursing standards and competencies to meet best practice expectations [35]. Unfortunately, these competencies have not been consistently incorporated into accreditation processes or curriculum revision initiatives and Canadian health and social service faculty are often unaware of published gerontological competencies that could aid them in curricular evaluation and optimization [36]. Barriers to integrating gerontological competencies include insufficient faculty expertise in gerontology and little recognition that gerontological competencies are needed [36]. If ageism was acknowledged, there would be a stronger impetus for implementing these competencies, thereby better serving older Canadians.

Against this background, scholars have identified that nurses are graduating with inadequate knowledge about working with older people [37–40], including how to care for them [26, 41]. Students observe what practitioners say and how they model care provision to older people, which can have a lasting impact on professional learning and socialization [42] and shape how student nurses learn to work with older people. Unfortunately, practicing nurses who demonstrate ageist behaviours towards older people unwittingly contribute to the professional socialization of students [24]. Our prior work revealed that practicing nurses and nurse educators often perpetuate student’ negative perceptions and pass on negative practices to the next generation of nurses [43]. For instance, when students witnessed nursing staff not listening to older people or neglecting to attend to their needs, the students inferred that these patients were not a priority, and that older patients’ concerns need not be addressed. Overall, students were not prepared for the complexity of the aging population, due to minimal curricular focus on older people, and lack of strong gerontologic role models [43]. Still, students wanted to learn more about aging and expressed interest in web-based and/or simulated learning activities. In another study, newly graduated nurses likewise identified the need for web-based learning activities that enhance knowledge about working with older people [44].

A critical review of the literature examining nursing education related to older people suggests that nursing programs have focused on integrating content about older populations into curricula, but not on the social aspects of learning processes that expose students to ageist perspectives and practices [45]. Certainly, students come from a wide range of cultures that contribute to socialization and beliefs about growing old, but they are also exposed to the negative stereotypes about aging embedded in nursing and healthcare cultures. Nursing programs reinforce uptake of these negative stereotypes and perpetuate ageism by privileging technical knowledge over gerontology-focused care [46]. Few nurse educators have gerontological expertise, which would enable them to actively dispel negative perceptions within nursing programs [37–39, 47]. Taken together, the dearth of gerontology-prepared nursing faculty, insufficient gerontological content, and learning experiences in nursing programs that perpetuate stereotypes of aging create negative care experiences for older Canadians.

### Study objectives and significance

A partnership with Canadian organizations that advocate for older people and the involvement of gerontological experts is needed to bring this awareness to the public and professionals that work with older people. Accordingly, we have the following three objectives:
To test if we can displace ageist perspectives, we will use student nurses as a test sample to determine if innovative e-learning activities aimed at dispelling aging myths improving students’ perceptions of older people and reduces negative stereotypes of growing old.To develop short-, medium-, and long-term strategies, based on the test results, aimed at dispelling negative stereotypes about aging in professional groups that serve older people and the Canadian public. An advisory group consisting of older Canadians and representatives from CanAge, HelpAge, Canadian Gerontological Nursing Association (CGNA), and academic gerontological experts will be assembled to tackle this challenge and identify appropriate methods to bring positive messages about aging to Canadians.To implement the short-term strategies developed by the advisory group. The specifics of the implementation plan will solidify as findings from testing the e-learning activities with student nurses and discussion with the advisory group are developed into strategies.

This project will improve how older people are treated in healthcare by creating awareness of ageism towards older Canadians, defined as people aged 65 and older [48]. Palmore [20] purports that the best way to reduce ageism is to bring awareness to it—our overarching aim—by developing strategies to dispel negative stereotypes about aging. We choose to address negative aging stereotypes in student nurses based on the findings of our previous research, but also because nurses, who are influential in healthcare teams, can model positive practice. If student nurses’ perceptions towards older people can be improved, other professionals and the Canadian public’s perceptions may be similarly improved to enhance service to older Canadians. Importantly, implementing the short-term strategies we develop will rapidly mobilize the initial research findings, but the project also has the potential to leverage relationships amongst the partners to implement medium- and long-term strategies.

### Theoretical framework: social learning theory

Bandura’s social learning theory which proposes that people learn new behaviours through observations in their social environments [32] will guide each step of this study. Social learning theory illuminates how people learn in society and proposes that behaviour and beliefs are often attributed to underlying forces that can be modified or eliminated with a new stimulus or learning approach. Student nurses, for example, learn in complex social environments that straddle classrooms and clinical settings, where they are exposed to healthcare professionals who may unconsciously be perpetuating negative behaviours towards older people [49]. Social learning theory will spur the project team to be attentive to the multiple ways that learning occurs (e.g., reading information, hearing information verbalized, observing the behaviour of others, etc.) and the importance social context plays in learning. The theory will direct our development of knowledge mobilization strategies to dispel negative stereotypes amongst Canadians and test student nurses’ perceptions about older people, following the e-learning activities, by focusing on the social aspects of how people learn, i.e., through the images they see, the messages they hear, and the behaviours related to ageing and older Canadians that are modeled for them. We propose that as student nurses’ perceptions improve and they acquire accurate knowledge, the current inadequate assessment and management of older people’s healthcare concerns, embedded as they are with ageist stereotypes, will dissipate [27, 29, 31]. Social learning theory will additionally guide us in analyzing the data, interpreting the findings, and knowledge mobilization, through careful attention to social contexts that influence how people perceive and behave towards older people.

## Methods/design

To raise awareness of ageism in Canada, this quasi-experimental study, supported by partnerships with older Canadians, advocacy organizations—Canadian Gerontological Nurses Association (CGNA) —gerontological nurses, and academic gerontological experts, will examine the effectiveness of e-learning activities on ageist attitudes then develop and implement strategies to combat such attitudes.

### Innovative learning approaches

In Phase one of this project, we will use innovative methods such as e-learning—education delivered on a digital device [50]—that incorporates gamification, videos, and simulation to convey positive perceptions of older people and non-ageist behaviours by healthcare professionals. A systematic review of the literature [51] found that that e-learning is an effective strategy for improving professionals’ knowledge, competence, and behaviours. Further, our literature review of web-based learning for nursing education revealed that gamification, simulation, and web-based virtual worlds are avenues that improve knowledge transfer and satisfaction with e-learning [52]. Gamification is defined as “the use of game design elements in non-game contexts” [53] p. 9 and is an engaging, interactive, and stimulating way to learn [54]. Nursing students identified that gamification increased their satisfaction with learning, stimulated creative thinking, and improved decision-making [55]. Virtual reality and self-directed e-learning, followed by practice in a virtual world, are also effective ways of acquiring new knowledge and skills [56–59].

Using e-learning activities to facilitate students’ development of positive perceptions of aging and gerontological expertise does not require instructors with academic expertise in those domains. Such change opens the possibility of improved interactions and outcomes for older Canadians. Moreover, if e-learning is an effective method for student nurses, it may be effective with other healthcare professions as well.

### Phase I (months 1 to 8): dispelling stereotypes (objective 1)

A quasi-experimental pre-post-test design will be used to test if the e-learning activities improve student nurses’ perceptions about older people—in particular, by dispelling stereotypes and providing positive role models for working with older people.

#### Setting and sample

The study will be conducted at two Canadian nursing programs to provide geographic variability of eastern and western Canada (York University and the University of Calgary). We estimate 1300 eligible students at York and 825 at U of C (total of 2125). Assuming a conservative 30% response rate, we anticipate a sample size of ~ 640 students. The sample size is estimated to attain adequate power to detect a small effect size of the e-learning intervention on student nurses’ perceptions about older people. Using Cohen’s [60] criteria of an anticipated small effect, a comparison among pre-and post-test scores and an α of .05 β set at .80, a minimum sample size of 393 is needed.

To maximize the response rate, Dillman’s [61] total survey method will be used. This method involves emailing eligible students a link to the e-learning activities and the survey. Non-responders will receive up to four email reminders, at two-week intervals after the first e-mail (i.e., three, five, seven, and nine weeks). A $10.00 gift card will be offered as an incentive for participating in each learning activity; this has been identified to increase survey completion rates [62].

#### Learning activities

To dispel negative stereotypes and ageism among student nurses, we will use three e-learning activities developed in our prior research [43] and previously tested with student nurses [63]. The topics of the activities were selected based on our prior work and target student nurses’ most urgent gerontological learning needs [43]. We will use games, videos, and simulations that model positive behaviours in the e-learning activities to spark interest and capture participants’ attention.

*Learning activity 1* will challenge negative stereotypes by providing information about healthy older Canadians and how to communicate with older people. Our previous research identified that student nurses lack knowledge about older people and how to communicate with them, which contributes to ageist perspectives [43]. We estimate participants will take 90 min to complete this activity.

*Learning activity 2* will focus on cognitive impairment (delirium, dementia, and depression), including positive modelling on how to manage anxiety and aggression in older people with these conditions. Previous research identified that student and practicing nurses do not feel equipped to work with older people with dementia [28, 43, 64, 65]. We estimate participants will take 3 h to complete this activity.

*Learning activity 3* will focus on dispelling stereotypes about older people as dependent and incontinent. Continence is a complex health issue influenced by cognition and physical ability, including mobility [66, 67]. Students nurses often hold negative stereotypes that incontinence is inevitable and believe it is not part of their job to help older people manage continence [68–70]. We estimate participants will take 90 min to complete this activity.

#### Data collection

Student nurses will complete a pre- and post-test using Burbank’s [71] measure of their perceptions about working with older people and the Ambivalent Ageism Scale (AAS) [4]; participants will also complete a post-test survey on their opinions of the learning activities. The pre- and post-e-learning activities will include the following three self-response scales:

Burbank’s Perceptions About Older People quiz [71] is a nine-item, 5-point Likert-type scale. The total score is derived by taking the mean of the responses. The higher the score out of five, the more positive the perception. This measure has demonstrated strong reliability and validity in previous studies [64, 72].

The Ambivalent Ageism Scale (AAS) is a 13-item, 7-point Likert-type scale, which measures benevolent and hostile attitudes towards older people [4]. The AAS provides a means to examine the complexity of ageism, including both positive and negative stereotypes measured by the benevolent (9 items) and hostile (4 items) ageism subscales, respectively. The subscale scores are derived by taking the mean of the responses. The overall scale has high test-retest reliability (r = .76) and internal consistency (a = .91). The reliability for the two subscales also demonstrated high test-retest reliability with benevolent (r = .71), hostile (r = .80) and internal consistency for the benevolent and hostile subscales (both α = .89).

*Post-learning activity survey* will be completed after each learning activity. The survey will include demographic questions and 5-point, Likert-type scale items measuring their perceptions about the learning activity.

To control for possible order effects in the survey responses, the sequence of the e-learning activities will be randomized using a computer-generated randomization scheme.

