#### Data analysis

Descriptive statistics will be used to describe participants’ average standing on all measured variables. We will use paired t-tests (after testing for assumptions) to compare participants’ pre- and post-test scores on Burbank’s quiz and the AAS subscales.

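### Activity order is randomised, but the stated paired t-tests do not use it; they give a valid package effect and no evidence on any single activity, although the article promises evidence on the three

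*Protocol article*

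**What the plan says.** All references are to the protocol article.

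- Phase I, design: "A quasi-experimental pre-post-test design will be used to test if the e-learning activities improve student nurses" in their perceptions of older people. No control or comparison group is described.
- Data collection: "To control for possible order effects in the survey responses, the sequence of the e-learning activities will be randomized" by a computer-generated scheme. No other purpose is given for the randomisation.
- Data collection, timing: the Burbank quiz and the Ambivalent Ageism Scale (AAS) are described as a pre-test and a post-test. Whether they surround the whole set or each activity is not said. Only the opinion survey is explicitly repeated; it "will be completed after each learning activity".
- Data analysis: "We will use paired t-tests (after testing for assumptions) to compare" participants' "pre- and post-test scores on Burbank’s quiz and the AAS subscales". Apart from descriptive statistics, this is the whole stated analysis.
- Abstract, contributions to the literature: "This study will generate evidence on the effectiveness of the three e-learning activities" on student nurses' perceptions of older people.
- Setting and sample: the sample size is justified for a small effect of the e-learning intervention as a whole.

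**The concern.** Sequence is the study's only randomised element, and the stated analysis makes no use of it. If there is one pre-test and one post-test, every student who finishes has had all three activities before the second measurement. The mean change is then a single blended figure.

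The activities differ in content. Activity 1 presents healthy older people and communication, activity 2 covers delirium, dementia and depression, and activity 3 covers dependence and incontinence. It is possible that one of them does nothing, or that showing impairment reinforces a stereotype while another activity weakens it. A blended change would hide either result. The advisory group in Phase II is to use the findings as a starting point for other professions and the public, so it matters whether they concern the set or its parts.

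The design makes this sharper. Without a control group, the pre/post change is open to testing and history effects. A comparison between randomised groups at the same time point shares those effects and so largely removes them.

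**Working it through.** **1. Does ignoring sequence make the planned test wrong?** Three activities give 3! = 6 possible orders. Assume all six are used equally, N = 640, and one change score per student with within-sequence SD 1. The pooled paired t-test was simulated 20,000 times with a true mean change of zero and a between-sequence SD of 0, 0.1, 0.2 or 0.3.

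| Between-sequence SD | Type I error, sequence ignored | Type I error, sequence in model |
|---|---|---|
| 0 | 4.8% | 4.8% |
| 0.1 | 5.0% | 5.0% |
| 0.2 | 4.4% | 4.8% |
| 0.3 | 4.2% | 5.2% |

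The planned test is not inflated; it becomes slightly conservative. The loss of precision is small. A standardised change of 0.200 falls to 0.2/√(1 + 0.3²) = 0.192 in the most extreme case, so a sequence term would shorten the confidence interval by about 4% (1 − 0.192/0.200).

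**2. Would a sequence term recover activity effects?** No. With one final post-test, all sequences contain the same three activities. Differences between sequences are order effects only. Activity effects need the scales to be measured between activities.

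**3. What could the randomised contrast detect if the scales were measured after the first activity?**

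Inputs:
- N: 30% of 2125 = 637.5, which the article rounds to about 640. One third is about 213 per first activity (equal allocation and no dropout assumed).
- Two-sided alpha .05 and power .80. The article gives .05 and .80 but not the number of sides.
- Pre/post correlation r: not given. The AAS test-retest values in the article (.71, .76, .80) are borrowed. No value is given for the Burbank quiz, so r = .5 is shown as well.

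Formula: detectable difference = (1.960 + 0.842) × √(2/n) × √(1 − r²), in SD units. For n = 213, the first two factors give 2.802 × 0.0969 = 0.2715.

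| r | √(1 − r²) | Detectable difference, n = 213 |
|---|---|---|
| .80 | 0.600 | 0.163 SD |
| .76 | 0.650 | 0.176 SD |
| .71 | 0.704 | 0.191 SD |
| .50 | 0.866 | 0.235 SD |

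A Bonferroni correction over the three pairs replaces 1.960 by 2.394. Every figure is then multiplied by (2.394 + 0.842)/2.802 = 1.155, which gives 0.188 to 0.221 SD for r = .80 to .71 and 0.271 SD for r = .5. Without baseline adjustment, power for 0.2 SD is 54%.

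At the article's minimum of 393 students (131 per first activity), the same formula gives 0.208 to 0.244 SD for r = .80 to .71.

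**The case against.** The strongest reply is that the question asked is about the package. The objectives, the Phase I design statement and the sample-size paragraph all speak of the activities or the intervention collectively, and the phrase in the abstract can be read the same way. Randomising the order also does its stated job by design. The sentence directly follows the description of the after-activity opinion survey, so it may be meant simply to balance fatigue and novelty in those ratings. Secondary models may sit in a fuller plan that is not shown.

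Most of this stands. There is no contradiction between randomising the order and using a paired t-test. Three stronger readings are tempting, and the documents do not support them:

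- *The t-test is biased or invalid because it omits sequence.* The simulation shows otherwise for one pair per student.
- *Activity effects are lost because sequence is left out of the model.* What decides this is when the scales are given; a sequence term alone would not bring those effects back.
- *Each student contributes up to three dependent pairs to one pooled test.* That would need scales around each activity and a pooled analysis. The article fixes neither, and separate tests per activity would escape the objection.

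Nor does the article say that all three activities would be rolled out on the strength of one p-value; the advisory group interprets the findings.

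What remains is that the promise in the abstract can be read per activity, that the stated analysis cannot deliver that reading, and that the timing of the scales, a design matter, is left unclear.

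**Conclusion.** The point holds in a limited form. The paired t-tests are sound for the package effect, within the limits of an uncontrolled pre/post design. They say nothing about any one activity, and they leave the only randomised element out of the analysis.

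The cost of omitting sequence is small: at most about 4% in interval width over the range simulated, and no check for order effects. The larger loss arises only if evidence per activity is wanted. A randomised first-activity contrast could then detect roughly 0.16 to 0.19 SD with about 640 students. This rests on borrowed AAS reliabilities, equal allocation and no dropout. The figure is about 0.235 SD at r = .5, and larger with multiplicity correction or attrition. It is therefore a useful secondary analysis, not a well-powered search for very small differences.

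**What to change.** **(a) In either case.** Include the randomised sequence as a factor in the change-score or baseline-adjusted model, alongside the paired comparison. This checks for order effects and may tighten the interval slightly. It does not estimate activity effects. It needs a line of analysis text and no new data.

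**(b) If evidence per activity is intended.** State when the Burbank quiz and the AAS are given. Add their 9 + 13 = 22 items to the survey already completed after each activity; if the existing post-test coincides with the third survey, this means two extra administrations. As secondary to the package pre/post test, report:
- the randomised, baseline-adjusted contrast after the first activity;
- a mixed model with activity, position and site as fixed effects and a student random effect.

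The cost is some response burden, repeated testing, and possible differential dropout by first activity, since activity 2 is estimated at 3 h and the others at 90 min each. Completion by first activity should be reported.

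**(c) If only the package effect is intended.** Reword the contribution in the abstract so that it claims the effect of the three activities together. This costs nothing.
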